## **Risks**

Specific risks associated with study-related procedures are described below. Measures taken to minimize risks are included within each section. Overall, the scientific benefit that this research project delivers outbalances the minor risks that the study procedures might put on individual subjects.

## Floating

Floating is a procedure employed for relaxation and stress reduction in many wellness centres around the world. It is generally considered very safe [8]. The water depth is around 25 cm and there is no risk of drowning even during sleep, since the high buoyancy of the saline allows effortless floating. In the control group (with lower salinity), water depth will be held around 10 cm.

Epsom-salt is non-toxic. Contact with the salty water can cause irritation of the eyes, mouth, nose and open wounds. Therefore, we will provide Vaseline to cover small scratches before floating. Inside of the tank there will be a damp cloth easily reachable for the subject.

The tank is equipped with an electric opening mechanism that can be operated from the outside and by the person inside the tank. The system is battery powered but the lid can still be opened in case of a system failure. Subjects can activate the light inside the tank or call the investigator via intercom by pressing one of three large buttons that are easily reachable.

Air circulation in the tank is ensured by thermal convection through an opening close to the face region and does not require any active components.

Water quality is assured by several factors: Subjects have to shower before entering the tank. The high salt levels of the water reduce bacterial growth to a minimum. The entire water of the tank is filtered automatically several times after each session and at the same time disinfected by an in-build hydrogen-peroxide/UV light sterilization unit. Water quality is monitored regularly by the principal investigator and water/salt will be changed after 200 floats.

Susceptible subjects may experience nausea, vertigo or disorientation in the tank that should, however, resolve spontaneously or by switching on the light inside the tank.

## Data analysis

All statistical analyses will be conducted using R (<https://www.r-project.org/>) and Python (<https://www.python.org/>). Pain and sensation drawings will be analysed with the FMRIB Software Library (<https://fsl.fmrib.ox.ac.uk/fsl/>).

The statistical test for the primary outcome will be a two-tailed two-sample t-test of the differences (before treatment - one week after treatment). In case of significant differences in the primary outcome measure at baseline, an ANCOVA model will be used instead. If the prerequisites for t-tests are not granted, we will use non-parametric tests to compare the differences. The study will be positive if we observe a significant difference ( $p < 0.05$ ) between the intervention and the control group.

For the secondary long-term outcomes we will use Chi-squared test (for the dichotomous condition) and mixed ANOVAs with between-subject factor "group" and within-subject factor "time" for the other outcomes. Secondary short-term outcomes will be assessed using two-tailed paired t-tests.

All outcomes will be assessed in an Intention-to-Treat (ITT) analysis under the following conditions:

- The subjects who drop out before the first session will be excluded from the analysis and replaced by other subjects.
- We will continue to acquire the endpoints, keeping the same time intervals, i.e. 1, 12 and 24 weeks after the last session.
- In the case that we cannot assess the endpoint due to missing data, the subject will be excluded from the analysis and replaced by another subject.

In order to test for the robustness of the therapeutic effect, we will also conduct per-protocol analyses afterwards.

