## Study Design

To investigate the therapeutic effects of floating and sensory deprivation on chronic pain we will divide the participants into three groups using a central randomization procedure.

- The **intervention group** will have the full floating experience: high buoyancy and maximal sensory deprivation.
- The **control group** will have a minimal floating experience designed as a placebo control. To achieve this we will manipulate the two mechanisms mentioned above: the water will have reduced buoyancy (low salinity) and there will be visual, auditory and somatosensory stimuli to reduce sensory deprivation to a minimum.
- The **no-treatment group** will be a waiting-list control. Patients in this group will not receive any treatment.

Our study will investigate short- and long-term effects of floating by evaluating separate endpoints after each floating session and after completion of the study (i.e. after five floating sessions).

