### Primary outcome (long-term):

The primary endpoint of the study is the reduction of pain (maximum and average) as measured by a numeric rating scale (NRS) retrospectively for one week.

**Secondary long-term outcomes** comprise improvements in

- 1.) Reduction of pain (maximum and average) by 30% or more (dichotomous)
- 2.) Pain-related disability (PDI)
- 3.) Trait Anxiety (STAI Trait)
- 4.) Depression (BDI)
- 5.) Quality of life (SF-12)
- 6.) Quality of sleep (NRS)
- 7.) Use of pain medication

**Secondary short-term outcomes** comprise improvements in

- 1.) Acute pain intensity (NRS)
- 2.) Acute pain area and widespreadness (from electronic pain drawing)
- 3.) State Anxiety (STAI State)
- 4.) Heart rate variability (improvement of sympatho-vagal balance indicated by an increase in HF- and a decrease in LF-HRV)
- 5.) Unusual bodily sensations during floating (electronic drawing)
- 6.) Altered states of consciousness during floating (5D-ASC)

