## Study population / Sample size calculation

Sample size calculation is based on a previous explorative studie [5] that showed significant differences between a treatment and a no-treatment group:

|             | Treatment (20) | No-treatment (17) |
|-------------|----------------|-------------------|
| Pain before | 61.75 ± 18.78  | 59.06 ± 17.68     |
| Pain after  | 37.25 ± 30.22  | 60.41 ± 17.21     |

With this number we compute the difference post-pre, which yields  $-24.50 \pm 35.58$  for the treatment group and  $1.35 \pm 24.67$  for the no-treatment group. These differences give a Cohen's d-value of 0.83.

For a two-tailed, two-sample t-test, it means that we need a sample size of 24 subjects per group ( $\alpha=0.05$ ,  $1-\beta=0.95$ , allocation ratio 1:1). To account for attrition we will recruit 25 patients per group, i.e. 75 in total. Drop-outs will be replaced should the size of any group drop below 24 patients.

Groups will be balanced for age, gender and average pain intensity (retrospective NRS rating of the last week), and subjects will be recruited according to the following criteria.

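### The primary analysis reaches ANCOVA only through a baseline significance test, so it will nearly always ignore baseline pain, age and gender and probably lose precision

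*Combined protocol and SAP*

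**What the plan says.** The Data analysis section sets a default: "The statistical test for the primary outcome will be a two-tailed two-sample t-test of the differences (before treatment - one week after treatment"). Two conditional replacements follow. The first is "In case of significant differences in the primary outcome measure at baseline, an ANCOVA model will be used instead". The second is "If the prerequisites for t-tests are not granted, we will use non-parametric tests to compare the differences". Success is judged on the intervention-versus-control comparison at p < 0.05.

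On allocation, Study Design says only that "we will divide the participants into three groups using a central randomization procedure". The sample size section adds "Groups will be balanced for age, gender and average pain intensity (retrospective NRS rating of the last week"). It names no method (stratified blocks, minimisation or other).

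Three details of the rule are not given: the level of the baseline test, the covariates of the ANCOVA, and what counts as failed prerequisites. The endpoint comprises maximum and average pain, and the rule does not say which score's baseline is tested. The analysis plan sits inside the protocol, and the opening page says the protocol was not altered after approval, so no later text in these documents settles these points.

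**The concern.** In a randomised trial, a baseline significance test examines a null hypothesis that is true by design. It says little about whether adjustment is worthwhile, which depends on how strongly baseline pain predicts later pain. Here the trigger is weaker still, because the groups are meant to be balanced on average pain. The adjusted model is therefore held behind a condition that the allocation is designed to prevent. The non-parametric fallback also compares unadjusted differences.

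Two things are at stake. The first is precision: a change score subtracts the whole baseline value, which adds noise unless the slope of follow-up on baseline is close to 1. The second applies only if balance is enforced at allocation. The t-test then counts baseline variation that can no longer contribute to the group difference, so its standard error is too large.

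**Working it through.** **Inputs from the sample size section.** Pain SD before: 18.78 (treatment, n = 20) and 17.68 (no treatment, n = 17). Pain SD after: 30.22 and 17.21. Mean changes: -24.50 and 1.35, a difference of 25.85. Planned size: 24 per group. The pre-post correlation r is not given and is assumed at 0, 0.3, 0.5 and 0.7.

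**Step 1: the plan's own figures.** √(18.78² + 30.22²) = 35.58 and √(17.68² + 17.21²) = 24.67, which are the stated change SDs. The plan has therefore added variances as if r = 0. The pooled change SD is 31.07, and 25.85/31.07 = 0.832, so the stated d of 0.83 reproduces. The stated 95% power does not: at d = 0.83, 24 per group gives about 80%, and 95% needs 39. That is a separate matter; it is noted here only because it fixes the starting point.

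**Step 2: variance ratio on the planning SDs.** Pooling within arms on 19 and 16 degrees of freedom:
- V_pre = (19 × 18.78² + 16 × 17.68²)/35 = 334.4 (SD 18.29)
- V_post = (19 × 30.22² + 16 × 17.21²)/35 = 631.2 (SD 25.12)
- C = r × 18.29 × 25.12
- Change-score variance = V_pre + V_post − 2C
- ANCOVA residual variance = V_post − C²/V_pre

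Power is from the noncentral t, two-sided 0.05, 24 per group, difference 25.85, with baseline pain as the only covariate.

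| Assumed r | Change variance | ANCOVA variance | Ratio | Power, change score | Power, ANCOVA |
|---|---|---|---|---|---|
| 0 | 965.5 | 631.2 | 0.65 | about 80% | 94% |
| 0.3 | 689.9 | 574.4 | 0.83 | 92% | 95-96% |
| 0.5 | 506.1 | 473.4 | 0.94 | 97% | 98% |
| 0.7 | 322.4 | 321.9 | 1.00 | equal | equal |

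The gain vanishes near r = 0.7 because the slope C/V_pre is then 321.6/334.4 = 0.96, so subtracting the baseline is nearly the best adjustment.

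If the pre and post SDs were equal, as they nearly are in the no-treatment arm (17.68 and 17.21), the ratio would be (1 + r)/2: 0.50, 0.65, 0.75 and 0.85 at the same r.

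**Step 3: how often the trigger fires, and the error rate.** Null trials were simulated with 24 per arm and equal pre and post SDs. The baseline test was set at 5%, which is an assumption.

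| Allocation | Trigger fires | Type I error of the change-score t-test at r = 0.3 / 0.5 / 0.7 |
|---|---|---|
| Simple randomisation | about 5% | about 5% throughout |
| Blocks within a median split of baseline pain | 0 to 0.2% | 2.8 / 3.4 / 4.2% |
| Random within pairs matched on baseline | 0% | 1.6 / 2.4 / 3.3% |

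ANCOVA held about 5% throughout. Under simple randomisation, the two-stage rule (t-test, or ANCOVA when triggered) ran at 4.1, 4.2 and 4.6%, so it too is slightly conservative.

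The matched-pair row can be checked by hand. With tight balance the true variance is close to the ANCOVA variance, so the effective critical value is 2.013/√((1 + r)/2). That is 2.50, 2.32 and 2.18, with two-sided tail areas on 46 degrees of freedom of about 1.6, 2.5 and 3.4%.

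**The case against.** The strongest reply is that the default is valid. Under simple randomisation the change-score t-test has the right standard error, and a positive result from it would stand. A reader might infer from the balancing statement that the intervals are certainly wrong. The documents do not support that: they promise balance but give no method, and tight matching is hard to achieve when patients are enrolled over time. With median-split blocks and roughly the planning SDs, type I error was 3.9, 4.8 and 4.8% at r = 0.3, 0.5 and 0.7, which is close to nominal. This stands, and the standard-error point is therefore conditional.

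A second reply is that the precision gain may be small. This also stands. The large gain at r = 0 rests on a value that comes from adding variances, not from evidence about r, and it is the value most favourable to ANCOVA among those in the first table. At r = 0.5 the power gain is about one point.

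A third reply is that the plan does name a default, a trigger and a fallback, so it would go too far to call the primary p-value undefined. That is right. What is missing is narrower: the level of the baseline test, the covariates, the prerequisite check and the score that triggers the switch.

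None of this favours the present rule. In the settings examined, ANCOVA kept its level and had equal or higher power.

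**Conclusion.** The point holds as a probable loss of precision caused by a trigger that serves no useful purpose. The primary analysis will be an unadjusted comparison of differences in about 95% of trials under simple randomisation, and in practically all trials if average pain is balanced at allocation. On the planning SDs the cost runs from about 14 power points at r = 0 to none near r = 0.7. The result depends on r, which the documents do not give, and on SDs from a treatment versus no-treatment comparison, whereas the primary contrast is floating against placebo floating.

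If balancing is enforced, intervals are also too wide and p-values too large. With equal SDs, type I error is about 3-4% with coarse strata and 2-4% with tight matching at r = 0.3 to 0.7. A reader might take a data-driven choice of model to mean excess false positives; the t-test/ANCOVA switch does not produce them here. Only average pain is balanced, so for maximum pain this part depends on its correlation with average pain.

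**What to change.** Drop the baseline significance test and prespecify one primary model: ANCOVA of the one-week pain score on group, the same score at baseline, age and gender, with the intervention-minus-control contrast tested at two-sided 0.05. When maximum pain is analysed, add baseline average pain, because that is the score used for balancing. State how balancing is carried out at allocation.

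Keep a rank-based or permutation test as a sensitivity analysis. A small-sample robust standard error is a reasonable optional addition there, since the planning SDs after treatment differ (30.22 and 17.21), but nothing in the documents makes it necessary for the primary test.

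No new data or patients are needed, because the baseline scores are already collected at the screening visit. The cost is a few degrees of freedom and a formal amendment: the analysis plan is part of the protocol, and the Amendments section sends every change to the ethics committee.

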## Endpoints

The study has **short-term endpoints** to assess the effect of each single floating session and **long-term endpoints** to assess the effect of a course of five successful floating sessions. While the former will be assessed before and after each floating session, the latter will be assessed one week after the final floating session and in two follow-ups at 12 and 24 weeks after completion. The only exception are pain area and widespreadness that will not be included in the follow-up assessments.

The study is successful, when the primary outcome shows significant differences between the intervention group and the control group at first assessment (one week after the final floating session).

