## Study procedures on each study day

The subject recruitment will start in February 2018 according to the inclusion and exclusion criteria and will be conducted at the Pain Outpatient Department (Schmerzambulanz) of the MHH.

At visit 1 (screening), written informed consent will be obtained. Subjects will undergo a physical examination and medical history taking. In- and exclusion criteria will be checked. Subjects will be familiarized with the floating tank. After this, the primary and secondary long-term outcomes will be assessed, as well as the expectancy/credibility rating.

At visits 2 - 6 (intervention), each separated by  $4 \pm 2$  days, in- and exclusion criteria will be checked again. Secondary short-term outcomes 1, 2 and 3 will be assessed. After this, a 5-minute ECG will be recorded for HRV analysis (short-term outcome 4). Subjects will then put on their bathing suits, take a shower and insert ear plugs before entering the floating tank (Tranquility, Floataway, Hingham, GB). The float itself will take 90 minutes. After the floating session subjects will leave the tank and take a shower to remove excess saline. Another 5-minute ECG will be recorded for HRV analysis (short-term outcome 4), before short-term outcomes 5 and 6 will be assessed.

After the last intervention, the subject is provided with a sealed envelope containing the questionnaires for the assessment of primary and secondary long-term outcomes and discharged.

On day 7 after visit no. 6 the subject is called by telephone and asked to fill out all questionnaires in the envelope and return it by mail.

This will be repeated at 12 weeks and 24 weeks after visit no. 6. Subjects in the intervention and control group will be unblinded after receipt of the last questionnaires.

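### The continuous secondary long-term outcomes are analysed without the visit-1 value as a covariate, which costs power for a sustained effect under each plausible reading of the mixed ANOVA

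*Combined protocol and SAP*

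**What the plan says.** - **Model.** Data analysis: "For the secondary long-term outcomes we will use Chi-squared test (for the dichotomous condition) and mixed ANOVAs with between-subject factor" group, with time as the within-subject factor. No covariate is named. The levels of time are not listed, and no term is named as the test of treatment.
- **Baseline.** Study procedures, visit 1: "After this, the primary and secondary long-term outcomes will be assessed". Each of these outcomes therefore has a pre-treatment value.
- **Follow-up.** Endpoints: "the latter will be assessed one week after the final floating session and in two follow-ups at 12 and 24 weeks after completion". That makes three follow-ups, or four levels of time if visit 1 is counted.
- **Definition.** The endpoint list says that the secondary long-term outcomes "comprise improvements in" disability, trait anxiety, depression, quality of life, sleep and medication use, alongside the dichotomous pain response. This wording is compatible with change scores but does not require them.
- **Primary outcome, for contrast.** Data analysis plans a "two-tailed two-sample t-test of the differences (before treatment - one week after treatment"), and adds: "In case of significant differences in the primary outcome measure at baseline, an ANCOVA model will be used instead". That clause covers the primary outcome alone, and only after a significant baseline difference.

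**The concern.** In a randomised trial with about 25 patients per arm, a patient's own baseline score is usually among the strongest predictors of later scores. The plan collects it for every secondary long-term outcome but never uses it as a covariate. The wording leaves four plausible analyses:

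1. Visit 1 is a level of time and the group main effect tests treatment.
2. Visit 1 is a level of time and group by time tests treatment.
3. Time covers the three follow-ups only, and visit 1 is unused.
4. The ANOVA is run on changes from visit 1.

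These can differ widely in power for the same true effect. With the tested term unnamed, the choice could also be made after the data are seen. A real effect on disability, mood, quality of life or sleep could be missed although the data to detect it are in hand.

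**Working it through.** **The plan's own figure.** The protocol gives no power for the secondary outcomes. Its sample size section covers the primary outcome only: d = 25.85 / 31.07 = 0.83, where 31.07 is the pooled SD of 35.58 (20 patients) and 24.67 (17 patients). The d reproduces. The 24 per group matches 80% power for a two-sided t-test (80.4%), not the stated 95%. That is a separate matter and is not used below.

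**Inputs.** From the documents: n = 25 recruited per arm, two-sided alpha 0.05, one baseline and three follow-ups. Assumed, because the documents do not give them: effect d in SDs of a single visit, and an equal correlation r between all visits. Intervention versus control, complete data, no expected difference at visit 1.

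**Variances per patient, in units of the single-visit variance**
- Mean of four levels: (1 + 3r)/4, with expected group difference (0 + d + d + d)/4 = 0.75d
- Mean of three follow-ups: (1 + 2r)/3
- Follow-up mean minus baseline: (1 + 2r)/3 + 1 − 2r
- Follow-up mean adjusted for baseline: (1 + 2r)/3 − r², times 47/46 for estimating the covariate

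The adjusted variance (before the factor 47/46) is smaller than the follow-up-only variance by r² and smaller than the change-score variance by (1 − r)².

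For the t-type tests the noncentrality is difference / √(2V/n), with 48 degrees of freedom (47 with the covariate). For group by time, λ = (n/2) Σ(δ_t − mean δ)² / (1 − r), on 3 and 144 degrees of freedom.

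**Sustained effect, d = 0.6 at all three follow-ups**
- r = 0.5: main effect 0.45/√(0.08 × 0.625) = 2.01; follow-ups only 0.6/√(0.08 × 0.667) = 2.60; change score also 2.60; adjusted 0.6/√(0.08 × 0.426) = 3.25; group by time λ = 12.5 × 0.75 × 0.36/0.5 = 6.75.
- r = 0.7: 1.81, 2.37, 3.35 and 3.77; λ = 11.25.

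| Power | r = 0.3 | r = 0.5 | r = 0.7 | r = 0.8 |
|---|---|---|---|---|
| Group main effect, four levels | 62% | 50% | 43% | 39% |
| Group by time, four levels | 42% | 56% | 80% | 94% |
| Follow-ups only | 81% | 72% | 64% | 61% |
| Change score | 58% | 72% | 91% | 98% |
| Follow-up mean, visit 1 as covariate | 87% | 89% | 96% | 99% |

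Keeping all three arms in the model gives the same pattern. With 24 per arm, d = 0.5 in the intervention arm only and r = 0.5, power is 36% (main effect), 39% (group by time) and 78% (adjusted).

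**Effect of 0.7 SD at one week only**
- Group by time: λ = 12.5 × 0.75 × 0.49/(1 − r) = 9.19 at r = 0.5 and 15.31 at r = 0.7. Power is 71% and 92%.
- Adjusted one-week contrast, variance (1 − r²) × 47/46: noncentrality 2.83 and 3.43. Power is 79% and 92%.
- Adjusted average over follow-ups: the difference is 0.7/3 = 0.23, so noncentrality is 1.26 and 1.47. Power is 24% and 30%.

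**A limit on the 89% and 96%.** They belong to the adjusted average. For the sustained 0.6 SD effect the adjusted one-week contrast alone has noncentrality 2.42 and 2.94, which is about 66% power at r = 0.5 and 82% at r = 0.7. At that single visit adjustment still helps: the variance is 0.75 against 1 for both the raw value and the change at r = 0.5, and 0.51 against 1 and 0.60 at r = 0.7 (before the factor 47/46).

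**The case against.** A mixed ANOVA with group by time is a conventional and valid analysis of a randomised pre-post design. Simulated null rejection rates for the methods compared were 4.2% to 5.9%, so nothing here inflates false positives. Success depends only on the primary outcome at one week, so this is a gain in efficiency for secondary outcomes. All of this stands.

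The size of the gain also depends on assumptions. No passage supports an undiminished effect up to 24 weeks. At high r, the change-score and group-by-time readings come close to the adjusted model. Averaging over follow-ups has its own cost: an effect that has gone after one week is cut to a third. This also stands, and it is why the fix does not make the average the main contrast.

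Two stronger readings are tempting, and the documents support neither:

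- A reader might infer that visit 1 can enter only as one more level of time. The plan does not list the levels. The endpoint wording allows change scores, and the primary test already uses them.
- A reader might infer that the treatment effect will be reported a quarter too small. That follows only if visit 1 is a level and the group main effect is taken as the treatment effect. The plan does not say so. The usual test in that layout is group by time, and its after-minus-before contrast is not diluted.

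**Conclusion.** The point holds as a worthwhile improvement at almost no cost, not as the correction of an invalid test. The plan names no baseline covariate for the continuous secondary long-term outcomes and leaves both the role of visit 1 and the tested term open.

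For a sustained effect, every reading has less power than adjustment for visit 1 at each correlation tried (0.3 to 0.8). With 25 per arm and 0.6 SD, the shortfall runs from 17 to 39 points at r = 0.5 and from 5 to 53 points at r = 0.7. For an effect at one week only, the gain over group by time is about 8 points at r = 0.5 and nil at r = 0.7. Shrinkage of the estimate to three quarters arises under one reading only.

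The correlations and effect sizes are assumptions. The calculation also assumes complete data and equal correlation between visits.

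**What to change.** In the Data analysis section, replace the mixed ANOVA for each continuous secondary long-term outcome with a model of the 1-, 12- and 24-week values. It should contain group, time, group by time and the patient's visit-1 value as covariate, whatever any baseline test shows.

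Name the intervention-control difference at one week as the main contrast, since that is the time point the Endpoints section uses for success. Report the 12- and 24-week differences and the average over the three follow-ups as supporting results. The average is the more powerful contrast if the effect lasts and the weaker one if it fades, so the order should be fixed before the data are seen.

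The cost is a change of wording and one degree of freedom per model. No new data or visits are needed.

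### For the six non-dichotomous secondary long-term outcomes, a mixed ANOVA with exclusion and replacement for missing data yields a completers analysis under an ITT label, if the time factor spans all the assessments

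*Combined protocol and SAP*

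**What the plan says.** The Endpoints section lists seven secondary long-term outcomes. One is dichotomous (pain reduction of 30% or more) and goes to a chi-squared test. The other six (PDI, STAI Trait, BDI, SF-12, sleep quality, use of pain medication) are assigned in Data analysis to "mixed ANOVAs with between-subject factor" group and within-subject factor time. The levels of time are not listed.

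The assessment times have to be taken from other text. Under Study procedures on each study day, baseline is taken in person at visit 1: "After this, the primary and secondary long-term outcomes will be assessed, as well as the expectancy/credibility rating". Endpoints says of the long-term outcomes that "the latter will be assessed one week after the final floating session and in two follow-ups at 12 and 24 weeks after completion". Under the study procedures, all three post-treatment assessments are questionnaires returned by mail, the first after a telephone call on day 7, and the procedure is repeated at 12 and 24 weeks.

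On the population and missing data, Data analysis says: "All outcomes will be assessed in an Intention-to-Treat (ITT) analysis under the following conditions". One condition is that endpoints continue to be collected, "keeping the same time intervals, i.e. 1, 12 and 24 weeks after the last session". Another is that where the endpoint cannot be assessed because of missing data, "the subject will be excluded from the analysis and replaced by another subject". No imputation or likelihood-based method is named. The sample size section has a different replacement rule: drop-outs are replaced only if a group falls below 24.

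**The concern.** A classical mixed (split-plot) ANOVA needs a value at every level of the within-subject factor. If the factor has four levels, a patient who returns the 1- and 12-week envelopes but not the 24-week one leaves the whole analysis, and the two returned questionnaires go unused. The exclusion rule in the same section points the same way.

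Two things are at stake. The first is validity. The analysis is called ITT but is restricted to patients who completed every assessment. If returning the questionnaire is related to how the patient responded, or to the arm, the group comparison can be biased. The second is efficiency: the plan commits to collecting data that this model cannot use. Because the row-completeness requirement comes from the model, repairing the missing-data rule for the primary t-test would not remove it.

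**Working it through.** **The plan's own figure.** The sample size section gives changes of −24.50 ± 35.58 (n = 20) and 1.35 ± 24.67 (n = 17). The difference is 25.85. The pooled SD is √[(19 × 35.58² + 16 × 24.67²)/35] = 31.07, so d = 25.85/31.07 = 0.83, as stated. A two-sided t-test at α = 0.05 with 24 per group has power 80.4% at d = 0.83; the stated 95% would need 39 per group. That discrepancy is a separate matter. It is noted here because 80.4% is the no-loss reference for the power figures below. The plan states no effect size or power for the mixed ANOVAs.

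**Inputs.** Three mailed returns per patient (study procedures) and 24 per group (sample size section). The documents give no attrition rate, so the non-return rate m per mailing is an assumption, shown at 5%, 10% and 15%.

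**Completers, independent non-return.** The fraction with all three returns is (1 − m)³. Completers per group without replacement are 24 × (1 − m)³. The number to randomise for 24 completers is 24/(1 − m)³. The share of returned questionnaires left unused is 1 − (1 − m)², because a returned questionnaire is used only if the other two also came back.

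| m | (1 − m)³ | Completers of 24 | Randomised per group for 24 completers | Returned questionnaires unused |
|---|---|---|---|---|
| 5% | 0.857 | 20.6 | 28.0 | 10% |
| 10% | 0.729 | 17.5 | 32.9 | 19% |
| 15% | 0.614 | 14.7 | 39.1 | 28% |

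The plan recruits 25 per group.

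**Power without replacement, as an illustration only.** This uses a two-sample t-test at a single visit with the primary outcome's d = 0.83 and two-sided α = 0.05. Available-data n is 24 × (1 − m).

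| m | Completers: n, power | Available at that visit: n, power |
|---|---|---|
| 5% | 20.6, 74% | 22.8, 78% |
| 10% | 17.5, 66% | 21.6, 76% |
| 15% | 14.7, 58% | 20.4, 73% |

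**Sensitivity to clustering of losses.** If the 12- and 24-week losses fall in the same patients, the fraction is (1 − m)². Completers are then 21.7, 19.4 or 17.3 per group, and power is 76%, 71% or 66%. If the same patients miss all three mailings, the fraction is 1 − m; completers equal available cases and the difference is nil.

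**Check on the group-by-time test itself.** A simulation used two groups of 25, four times, correlation 0.5 treated as known, an effect of 0.83 on the change scale at every post-treatment visit, loss completely at random, and 1,500 runs. At 5%, 10% and 20% missing per mailing, power was 78%, 72% and 52% on complete cases and 85%, 83% and 82% on all available data, against 85% with nothing missing. Treating the correlation as known slightly flatters the available-data analysis. Type I error at 10% missing was 6.0% on complete cases and 4.9% on available data.

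**The case against.** A reader might infer that the plan necessarily loses power. The documents do not support that. The sentence that excludes a subject also replaces that subject, and the sample size section tops up any group that falls below 24. If replacement is carried out, the number analysed is restored and the no-replacement figures do not apply. This part of the objection stands, and power loss should not be presented as automatic.

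Replacement does not answer the rest. A replacement enters the analysis only by passing the same completion filter, so the excluded randomised patients are not recovered, and any bias from selective non-return is reproduced. A missing 24-week return is known only about six months after the last session. The two replacement rules also differ, so the text does not settle how many subjects would be replaced.

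A reader might also take it as stated that a missed 24-week envelope removes the 1-week data. It is not. The time levels and whole-patient exclusion are inferences: separate baseline-versus-visit ANOVAs, or exclusion by outcome and visit, would fit the wording. But no other long-term assessment times are named, and a single classical mixed ANOVA over all of them could not exclude by visit.

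It is fair, too, that d = 0.83 comes from a pain change score against no treatment and has no stated bearing on PDI, STAI, BDI, SF-12, sleep or medication use, and that independent non-return is the less favourable pattern. The telephone prompt may keep losses low. Hence the power figures are only an illustration.

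Lastly, the point does not reach the success criterion. The primary is a two-sample comparison at one week, which a missed 12- or 24-week return does not affect.

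**Conclusion.** The concern holds, conditionally, for six secondary outcomes. If the time factor covers baseline, 1, 12 and 24 weeks, the planned analysis is a completers analysis labelled ITT and leaves observed data from randomised patients unused. With replacement, the cost is extra recruitment (about 28, 33 or 39 randomised per group instead of 25, at 5%, 10% or 15% independent non-return) and a comparison no longer protected by randomisation. Without replacement, the cost is a fall to 20.6, 17.5 or 14.7 completers of 24; in the single-visit illustration, completers give up about 4, 10 or 15 points of power relative to available data. The gap shrinks as losses cluster in the same patients and vanishes if they miss all three mailings. The non-return rates are assumptions throughout. The change is worth making, but the point does not call the primary analysis into question.

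**What to change.** For these six outcomes:

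- Replace the mixed ANOVA with a likelihood-based linear mixed model for repeated measures on all observed post-baseline visits. Include group, visit, group-by-visit and the baseline value as covariate. State the within-patient covariance structure and the small-sample degrees-of-freedom method.
- List the visits in the model, and report the group difference at 1, 12 and 24 weeks from it.
- Delete the exclude-and-replace rule for these outcomes, and keep every randomised patient with at least one post-baseline value in the assigned group. If the rule stayed, it would still strip patients with partial data from the new model.
- Reconcile the replacement rule in the sample size section with the one in Data analysis.

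The cost is SAP wording and a few lines of R, which the plan already names; no extra patients or data are needed. The model relies on missing-at-random, which is weaker than what a completers analysis assumes but cannot be verified from the data. Patients with no post-baseline value still contribute nothing to the estimates, so their number should be reported by group.
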